# Evaluation of a transdiagnostic mental health intervention in German primary care: study protocol for a parallel-group, two-arm, cluster randomised controlled pilot study

**DOI:** 10.1186/s40814-025-01597-6

**Published:** 2025-01-31

**Keywords:** Primary Care, Family Medicine, General Practitioner, Transdiagnostic approach, Unified Protocol, Brief Psychological Intervention, Psychoeducation, Mental Health, Pilot Study, Randomised Controlled Trial

## Abstract

**Background:**

General practitioners play an important role in the first-line care of individuals with mental health conditions. However, factors such as time constraints, limited experience in managing mental health conditions and high rates of comorbidity may hinder adequate treatment. To improve psychological care, adopting a transdiagnostic approach shows potential. Research on transdiagnostic interventions delivered by general practitioners is scarce. Thus, a transdiagnostic intervention adapted from the Unified Protocol for Transdiagnostic Treatment of Emotional Disorders was developed specifically for primary care. In a parallel-group, two-arm, cluster randomised controlled pilot study, the transdiagnostic intervention will be evaluated for feasibility, acceptability and potential effectiveness in German primary care.

**Methods:**

A total of 100 adult patients with a mental health condition will be recruited by general practitioners. In the intervention group, general practitioners will administer the transdiagnostic intervention, introducing patients to psychological concepts based on transdiagnostic factors (i.e., understanding emotions, cognitive flexibility, countering emotion-based avoidance). In the control group, general practitioners will provide improved treatment as usual oriented on official German treatment guidelines for depression, anxiety and somatoform disorders. In both study groups, treatment will be carried out in four 20-min sessions over 12-weeks. Self-report questionnaires will be completed before treatment initiation (only patients) and after treatment completion (patients and general practitioners) to assess feasibility and acceptability (i.e., treatment recruitment, delivery, response, effectiveness, unintended consequences and maintenance) as well as potential effectiveness (i.e., change in transdiagnostic factors).

**Discussion:**

The pilot study will address the research gap concerning general practitioner-led psychological interventions in primary care and will give insights into whether the adoption of a transdiagnostic approach is of benefit to general practitioners and patients. Findings may inform the design of a main trial by identifying barriers to the transdiagnostic intervention’s feasibility and acceptability, whilst advancing treatment delivery protocols to support effectiveness.

**Trial registration:**

The protocol for this study has been registered with the German Clinical Trials Register: DRKS00033386, Date of registration: 18^th^ of March 2024, https://drks.de/search/en/trial/DRKS00033386.

**Supplementary Information:**

The online version contains supplementary material available at 10.1186/s40814-025-01597-6.

## Background

Mental health conditions are highly prevalent worldwide [1]. The general practitioner (GP) is typically the first and sometimes only point of contact for affected individuals [2, 3]. However, the management of mental health conditions in primary care (PC) is often inadequate [3, 4]. This may be related to short appointment times [5] and limited training of GPs in psychological care [6, 7]. Another contributing factor could be how mental health conditions present in PC, being characterised by a less specific but rather dimensional manifestation of symptoms (e.g., various degrees of depressive and anxious symptoms) [8] and a high comorbidity rate [9–11]. Diagnosing according to ICD [12] or DSM [13] criteria and subsequently delivering a specialised treatment, as is common in the psychological and psychiatric setting, might therefore be unfeasible for GPs [3, 6, 7, 14]. To meet the contextual demands of PC [3] and to improve first-line psychological care - bridging the timespan to more specialised psychological or psychiatric services - the use of a transdiagnostic approach may be promising [6, 15].

In contrast to disorder-specific diagnosis and treatment, the transdiagnostic approach operates across or beyond diagnostic categories. The focus is thus shifted from differences between mental disorders to their similarities, so that shared mechanisms (i.e., transdiagnostic factors) can be identified and used for assessment and treatment [16]. To date, research on transdiagnostic treatments administered by GPs is scarce. The majority of previous psychological interventions in PC have taken a disorder-specific perspective [17–19]. In studies focusing on multiple mental disorders, the involvement of GPs was mostly limited to screening, while treatment was provided by others (e.g., study nurses, psychotherapists, study nurses). Only four studies were identified that focused on treating multiple mental disorders of individual PC patients and were delivered exclusively by GPs [20–23]. In two studies, GPs were trained to provide better care for stress-related mental disorders [20, 23], while GPs of the other two studies administered structured problem-solving and/or cognitive behavioural therapy (CBT) [21, 22]. The small number of studies, combined with heterogeneity in treatment methods and effects, warrants further evaluation of a transdiagnostic treatment approach in PC.

Among transdiagnostic approaches, the Unified Protocol for Transdiagnostic Treatment of Emotional Disorders (UP) [24] has the largest evidence base [25] and was successfully implemented in a wide range of settings [26]. It identifies neuroticism (i.e., the frequent experience of negative emotions) accompanied with the negative appraisal of undesirable emotions and dysfunctional forms of coping as the underlying mechanisms of “emotion-based disorders” (e.g., mood and anxiety disorders) [27, 28]. Guided by principles of CBT, the UP aims to educate individuals about emotional experiences (module 2) and introduces psychotherapeutic concepts, including mindfulness (module 3), cognitive flexibility (module 4), countering emotion-based avoidance/situational exposure (module 5/7) and interoceptive exposure (module 6) [29, 30].

To comply with recommendations for psychological interventions in PC (i.e., four to six sessions of no more than 30 min each [3]) a shortened UP-based treatment approach was developed, comprising four 20-min sessions. Previous research has shown that the delivery of a subset of UP modules, or even a single module, can already achieve symptomatic improvements [29, 31–33]. Due to the interrelated nature of the UP modules, assigning a clear therapeutic superiority to any one module is difficult [34]. Research suggests the relevance of each UP module and its targeted transdiagnostic factor across a range of mental disorders [35–37], with the exception of interoceptive exposure (i.e., confronting bodily sensations such as a racing heart), which is particularly supported for anxiety-related disorders [38, 39]. For PC, the effectiveness of cognitive reappraisal (i.e., developing greater flexibility in thought patterns) and behavioural activation/exposure (i.e., engaging in pleasurable activities/countering avoidant tendencies) as psychotherapeutic approaches has been indicated [6, 40]. Thus, considering both effectiveness and practicability, the UP modules on cognitive flexibility (module 4) and countering emotion-based avoidance (module 5) were selected as core sessions of the treatment. In addition, the UP module on understanding emotional experiences (module 2) was chosen as an introductory session to provide patients with a coherent treatment structure [41].

The objective of the cluster randomised controlled pilot study will be to evaluate the UP-based transdiagnostic intervention in German PC as compared to improved treatment as usual (iTAU). The primary aim will be to assess feasibility and acceptability in terms of patients’ and GPs’ perceptions of treatment recruitment, delivery, response, effectiveness, unintended consequences and maintenance. The secondary aim will be to evaluate potential effectiveness by monitoring patients’ trajectories in transdiagnostic factors (i.e., beliefs about emotions, experiential avoidance, emotion suppression, cognitive reappraisal and negative affectivity) as surrogate outcomes for mental health improvement.

## Methods

### Design

The pilot study will adopt a parallel-group, two-arm, cluster randomised controlled design. It adheres to the CONSORT statement extension to randomised pilot and feasibility trials [42] and to the SPIRIT guidelines [43] (Additional file 1). Using a 1:1 allocation ratio on PC practice level, GPs will provide patients with either a transdiagnostic intervention (i.e., intervention group (IG)) adapted from the UP [24], or with iTAU (i.e., control group (CG)) based on official German guidelines for the treatment of a depression, anxiety or somatoform disorder [44–46]. In both study groups, treatment will consist of four 20-min sessions administered over 12 weeks. Data collection will take place at baseline (patients only) and after treatment completion (patients and GPs) (Fig. 1).

**Fig. 1 Fig1:**
[figure not shown]
Study design and participant flow according to CONSORT

### Population and setting

A total of 100 German adult PC patients with a mental health condition will be recruited by GPs from 20 PC practices within the region of Munich, Germany.

#### Eligibility criteria

Patients will be eligible if they (1) are fluent in German, (2) are at least 18 years old, (3) have a mental health condition as assessed by GPs (assisted by the Kessler-6 (K-6) [47]) and (4) provide written or digital informed consent prior to participation.

GPs will assess the following exclusion criteria by interviewing patients and reviewing their medical record: (1) Life expectancy ≤ 12 months, (2) known substance use disorder (e.g., alcohol, illegal drugs or medication; excluding nicotine dependence), (3) increased risk of suicidality, (4) having a cognitive impairment (e.g., dementia), (5) suffering from a mental disorder of great severity that warrants more intensive, specific treatment (e.g., severe depression, bipolar disorder, borderline disorder, schizophrenia, anorexia), (6) receiving psychotherapy at study start, (7) in case of psychotropic drug use, a change in medication intake in the 6 weeks prior to study start and (8) not being able to visit the PC practice for the treatment in person due to physical impairments.

GPs will be eligible if they (1) have a qualification in psychosomatic care, or alternatively have completed additional psychiatric training, and (2) provide written informed consent.

#### Recruitment

PC practices will be recruited through the teaching practice network of the Institute of General Practice at LMU Munich and with flyers sent to GPs registered with the “Kassenärztliche Vereinigung” and/or the “Bayerische Landesärztekammer”. After a GP declares their interest to participate, inclusion criteria for GPs will be confirmed in a telephone call. If a GP meets the inclusion criteria, an appointment will be scheduled in which a member of study staff will visit the practice to explain all treatment details and the procedure of the study as well as to obtain informed consent (t_-1_).

GPs will recruit study participants from their pool of new and on-going patients. The identification of patients with a mental health condition will be based on a GP’s overall impression of a patient, assisted by a short questionnaire on general psychological distress (i.e., K-6 [47]). For the latter, GPs are provided with age-specific German norm values for the K-6 [48]. Eligibility will be confirmed by GPs with a checklist, covering all inclusion and exclusion criteria.

#### Randomisation

Once at least one GP of a PC practice agrees to participate, cluster randomisation will be conducted at practice level as per a computer-generated sequence in a 1:1 ratio. This approach was chosen to prevent spillover effects within clusters, such as when several GPs from one practice participate in the study [49]. To ensure an even distribution of patients between IG and CG, randomisation will be stratified by the number of GPs in a practice providing treatment, assuming that practices with more participating GPs will treat more patients. As part of the consecutive recruitment, for each practice stratum (e.g., two participating GPs per practice), the first practice recruited is randomly allocated to either the IG or CG using the RANDBETWEEN function in Microsoft Excel [50]. This function generates an integer within a specified range (e.g., 1 or 2), with each value having an equal probability of being selected, thereby ensuring fairness in allocation. Within one stratum, the next recruited practice will be assigned to the opposite study group, and so forth. If a study group is underrepresented when a stratum is newly formed (i.e., more practices have been assigned to either study group overall), this study group will be prioritised for allocation to prevent imbalance in the distribution of practices.

Randomisation will be managed and documented by a staff member of the Institute of General Practice at LMU Munich, who is not part of the study [50]. Allocation concealment will be maintained using opaque envelopes, which will be opened by study staff only shortly before GPs are trained in their assigned treatment condition.

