#### Sample size

No formal sample size calculation is required for a pilot study [51]. To minimise the maximum likely error for any calculated rates to less than 10%, Eldridge et al. [52] suggested a total of 23 clusters for cluster-randomised pilot studies with a cluster size of five participants, assuming an intra-cluster correlation (ICC) of 0.05. Similar ICCs were found for psychological outcomes in German PC [53] and recruiting six patients per PC practice was considered feasible for psychological interventions [54, 55]. To balance scientific considerations and practical constraints (i.e., time and staff resources), a sample size of 100 patients across 20 PC practices is anticipated, with six patients enrolled per practice, accounting for an expected 20% dropout rate. This should provide sufficient data to adequately assess treatment feasibility, acceptability and potential effectiveness, forming a robust basis for a confirmatory main trial.

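### Allocation of practices is described as a concealed computer-generated sequence, but the stated rule is alternation within strata after a random start

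*Protocol article*

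**What the plan says.** The Randomisation section of the protocol article makes a general claim: "cluster randomisation will be conducted at practice level as per a computer-generated sequence in a 1:1 ratio". It adds that "randomisation will be stratified by the number of GPs in a practice providing treatment", so that patients are spread evenly between the arms.

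It then gives the mechanism. In each stratum, "the first practice recruited is randomly allocated to either the IG or CG using the RANDBETWEEN function in Microsoft Excel". For the practices that follow, "Within one stratum, the next recruited practice will be assigned to the opposite study group, and so forth". There is one override: "If a study group is underrepresented when a stratum is newly formed", then "this study group will be prioritised for allocation to prevent imbalance in the distribution of practices".

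On concealment: "Allocation concealment will be maintained using opaque envelopes, which will be opened by study staff only shortly before GPs are trained". A member of the institute who is outside the study manages and documents the allocation. The Recruitment section has study staff visit each practice, explain the study and obtain the GPs' consent. The Blinding section states that study staff cannot be blinded to allocation.

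**The concern.** The general claim and the mechanism do not agree. A random sequence gives each practice an arm that earlier arms do not fix. Under the stated rule, every practice after the first in its stratum receives an arm that follows from the one before it. This is not a detail left to a fuller document, because the article states the rule outright.

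The rule also undercuts the envelopes. The stratum is the number of participating GPs, which must be known before allocation. The people who consent practices also open the envelopes. Once they have opened one envelope in a stratum, they can work out what the next one in that stratum contains.

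At stake is the protection that randomisation gives against selection of practices. Someone who can foresee the arm could influence when a practice is enrolled or how many GPs it declares. The article calls the trial cluster randomised, compares the arms with group-by-time mixed models, and wants the results to support the design of a main trial, which might inherit the procedure.

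**Working it through.** The plan gives no figure for predictability, so there is none to reproduce. The check applies the written rule.

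**Inputs**
- Practices: N = 20. The Sample size section says "a sample size of 100 patients across 20 PC practices is anticipated, with six patients enrolled per practice".
- Strata: defined by the number of participating GPs. Their number and frequencies are not stated, so k = 1 to 5 is assumed with several frequency patterns.
- First practice in a stratum: a fair draw if the arms have equal totals at that moment, otherwise the smaller arm. This reads prioritised as always.
- Every later practice in the stratum: the arm opposite to the previous one.

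**Step 1: two strata by hand.** Take shares 0.7 and 0.3. The very first practice is drawn at random. The first practice of the second stratum is drawn at random only if the first stratum holds an even number of practices by then.
- The first stratum to open is the common one (probability 0.7): P(even) = 0.7 × 0.3 / (1 − 0.7²) = 0.21 / 0.51 = 0.412.
- It is the rarer one (probability 0.3): P(even) = 0.3 × 0.7 / (1 − 0.3²) = 0.21 / 0.91 = 0.231.
- Expected random draws: R = 1 + 0.7 × 0.412 + 0.3 × 0.231 = 1.36.

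**Step 2: simulation of the rule**, 40,000 runs per pattern. The determined share is 1 − R/20. Someone who knows all past allocations is right on every determined one and on half of the random ones, so the share of correct guesses is (20 − R/2)/20.

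| Assumed strata | Mean R of 20 | Determined | Correct guesses |
|---|---|---|---|
| 1 | 1.00 | 95.0% | 97.5% |
| 2 (0.7, 0.3) | 1.36 | 93.2% | 96.6% |
| 3 (0.6, 0.3, 0.1) | 1.74 | 91.3% | 95.7% |
| 3 (equal) | 1.77 | 91.1% | 95.6% |
| 4 (0.5, 0.25, 0.15, 0.1) | 2.10 | 89.5% | 94.8% |
| 4 (equal) | 2.16 | 89.2% | 94.6% |
| 5 (equal) | 2.52 | 87.4% | 93.7% |

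The two-stratum row agrees with the hand calculation.

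**Step 3: bounds.** R cannot exceed the number of strata. With 5 strata, all opened when the arms are equal, 1 − 5/20 = 75% are still determined. This bound also covers a softer meaning of prioritised, in which the first draw in a stratum keeps some random element. If the text meant a fresh draw for every pair, 50% would be determined and 50% + 50%/2 = 75% guessed correctly.

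**Step 4: comparison with a random list**, one stratum of 20 practices, with the guesser always naming the arm that is behind. Permuted blocks of 4 give about 71% correct guesses, random sizes 2 and 4 about 72%, and random sizes 4 and 6 about 69%. Simple randomisation gives 50%. The written rule gives 97.5% in the same one-stratum setting.

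**The case against.** Several points on the other side are sound.

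- **The envelopes are not worthless.** A reader might infer that they conceal nothing. That goes too far: they hide the random first draw of a stratum, they hide the arm from GPs who know nothing of earlier allocations, and they hide an allocation made before the previous envelope in that stratum has been opened. Allocation also follows the GP's agreement to take part, which limits selection by the GP.
- **Determined is not the same as foreseen.** A reader might infer that staff know 87% to 95% of allocations with certainty. The documents do not support that. Envelopes are opened late, an outside staff member runs the process, and the article does not say how far recruitment and training overlap. The percentages count what the rule fixes, so they are an upper limit on what staff can foresee.
- **No steering is documented.** Practices volunteer through a teaching network and flyers. Delaying a volunteer or adjusting the declared number of GPs is possible, but nothing shows that it happened, and the size of any bias cannot be estimated from the article.
- **This is a pilot.** Feasibility and acceptability scores are presented graphically, no progression thresholds are set, and effect estimates are reported with confidence limits only. Unblinded GPs also select the patients, and a better list for practices does not change that.

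These points limit the consequences. They do not make the stated rule a random sequence, and the pairwise reading that would soften it is not what the text says, since it draws only for the first practice recruited in a stratum.

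**Conclusion.** The point holds in a bounded form. The Randomisation section claims a computer-generated sequence with concealment, while its own rule is alternation within strata after a random start, with an override that can remove even the random start. On average about 1 to 2.5 of the 20 allocations are random.

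This size rests on an assumed 1 to 5 strata, on assumed stratum frequencies, and on prioritised meaning always. The least favourable case relaxes the last two and still leaves three quarters of the allocations fixed by earlier ones. The consequence is weakened protection against selection of practices in between-arm comparisons. It is not evidence that selection took place.

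**What to change.** **Practices not yet allocated, and the main trial.** Replace the alternation and the override with a list prepared in advance and held by the staff member outside the study. Use either permuted blocks of randomly varying size within a few GP-number strata, or minimisation with a random element. Withhold the block sizes from study staff. Release each arm only after the practice and its number of participating GPs are registered.

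**Practices already allocated.** Report alternating allocation after a random start within strata. Withdraw the claim of a computer-generated sequence for them, qualify the concealment claim, and name this as a limitation of between-arm comparisons. This step remains possible at any stage. It may be the main one, since patient recruitment ran from 1 June 2024 to 31 March 2025 and the article appeared on 31 January 2025.

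**Cost.** Generating a list is quick, but there are three drawbacks.
- Balance: with two strata and blocks of up to 4, each stratum can stop mid-block with a difference of 2, so the arms could differ by 2 + 2 = 4 practices (12 against 8). Under the current rule the simulated maximum was 2 with two or three strata and 4 with four or five.
- Predictability: blocks of 2 and 4 still allow about 72% correct guesses, against 94% to 98% now.
- A mixed scheme: changing the method part-way leaves two allocation methods in one trial, and both must be reported.

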#### Blinding

Due to the design of the study, it is not possible for GPs, patients or study staff to be blinded to the study group allocation. However, participants will be blinded to which of the two treatments is considered the active intervention.

